### Assignment of interventions

4.8

Once participants have completed T1 they will be randomly allocated to the control or intervention arm. Randomisation will be allocated on a 1:1 ratio in blocks of four, without stratification. The allocation sequence will be created using a pseudo-random algorithm in Stata (17.0, StataCorp LLC, College Station, TX) with a true random seed number between 1 and 1,000,000 [35]. The allocation sequence will be executed in Research Electronic Data Capture (REDCap, Version 13.7.31, Nashville, Tennessee, USA). Research team members who enrol participants in the respective study arms will not have access to the randomisation details.

Participants cannot be blinded to treatment allocation given the intervention type. All members of the research team will be blinded except for the research assistants. Unblinded staff will enrol participants, assign participants to the control or intervention arms as per the treatment allocation sequence generated, inform participants of the study requirements according to intervention/control group allocation and be the main contact point for participants. Unblinded staff will not analyse data. The research team member who creates the randomisation sequence will not contact participants, nor administer data collection. All other research team members (investigators, data analysts, postgraduate students) will be blinded. The need to unblind other research team members is unlikely.

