### Sample size

4.6

At least 345 participants will be randomly allocated across both study arms—an oversampling of 15 % to allow for attrition (based conservatively on *trips4health* and the relevant ACHIEVE study [12,18]) leaving a minimum of 300 participants. Three hundred participants will provide 80 % power (two-sided α = 0.05) to detect a 34 % change (∼2500 steps/day) in daily steps in the intervention group relative to controls (primary outcome) and meaningful increases (13–29 %) in secondary outcomes. The power calculation is based on the standard deviation of change in the physical activity outcomes, log-transformed due to the right-skewed nature of physical activity data (Table 3).

**Table 3 tbl3:** Increase in outcomes detected with n = 300.

Outcomes	Standard deviation of change (log scale)^a^	Relative increase in outcome
Accelerometer (steps/day)	0.336	11.5 %
Transport-related physical activity (hours/week)	0.790	29.1 %
Bus use in week (trips/day)	0.390	13.4 %

a Standard deviation estimates from *trips4health*.

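### A fixed block size of four could let unblinded enrolling staff who know it deduce up to about one third of allocations

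*Protocol article*

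**What the plan says.** Everything at issue stands in section 4.8 (Assignment of interventions) of the protocol article, apart from the sample size in section 4.6.

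- **List structure:** "Randomisation will be allocated on a 1:1 ratio in blocks of four, without stratification". There is therefore one list, and every block has the same length.
- **Who is unblinded:** "All members of the research team will be blinded except for the research assistants".
- **What they do:** "Unblinded staff will enrol participants, assign participants to the control or intervention arms as per the treatment allocation sequence generated". They also explain to participants what their arm involves and are their usual contact.
- **Safeguards:** "Research team members who enrol participants in the respective study arms will not have access to the randomisation details". The list is generated in Stata and run in REDCap, and "The research team member who creates the randomisation sequence will not contact participants, nor administer data collection".
- **Timing:** "Once participants have completed T1 they will be randomly allocated to the control or intervention arm".
- **Size (section 4.6):** "At least 345 participants will be randomly allocated across both study arms".

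The article does not say that block sizes vary, or whether the block size is among the details withheld from enrolling staff.

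**The concern.** Concealment has two parts: nobody who enrols should see the list, and nobody who enrols should be able to work out the next entry. The stated safeguards deal with the first. The second is weak here because three features coincide: a short block of constant length, a single list without strata, and open allocation handled by the people who enrol. Someone who knows that blocks hold two of each arm, and who has followed the order, knows the last place in every block and sometimes the one before it.

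At stake is selection bias. Participants know their arm and the outcomes are behavioural, so readiness to change could affect both bus use and steps. If more willing people tended to be moved forward when the incentive arm was due, part of the difference between arms would reflect who entered them. Staff who are the usual contact during T1, with its mailed accelerometer, survey and travel diary, can have some effect on who finishes T1 and in what order.

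**Working it through.** The article gives no figure for predictability, so there is none to reproduce. The inputs are a 1:1 ratio, a block size of 4 and one list (section 4.8), and 345 randomised (section 4.6).

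**1. Places known with certainty.** A block has six equally likely orders: AABB, BBAA, ABAB, ABBA, BAAB, BABA. A place is forced when one arm is already used up.

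- AABB and BBAA: places 3 and 4 are forced, giving 2 × 2 = 4.
- The other four orders: place 4 only, giving 4 × 1 = 4.
- Total: 8 of 24 places = 33.3%.

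Equivalently, place 4 is always forced and place 3 is forced with probability 1/3, so 1 + 1/3 = 4/3 of every 4. For a block of size 2m, the share is 1/(m + 1): 1/3 for size 4, 1/4 for size 6 and 1/5 for size 8.

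**2. Applied to this trial.** 345 = 86 × 4 + 1, so there are 86 full blocks. Expected forced allocations = 86 × 4/3 = 114.7, about 115 of 345 (33.2%).

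**3. Success of best guessing.** The probability of a correct best guess is:

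- place 1: 1/2
- place 2: 2/3
- place 3: 1/3 × 1 + 2/3 × 1/2 = 2/3
- place 4: 1

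The mean is (1/2 + 2/3 + 2/3 + 1)/4 = 17/24 = 70.8%, against 50% under simple randomisation.

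**4. Randomly varying sizes.** For each design, 400 lists of 345 were simulated, with an observer who knows the set of sizes but not their order and who updates after each allocation. Run on fixed blocks of four, the simulation returned 33.3% and 70.8%, matching the exact values.

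| Block sizes | Known with certainty | Best guess correct |
|---|---|---|
| Fixed 4 | 33.3% | 70.8% |
| Random 4, 6 | 5.4% | 69.2% |
| Random 4, 6, 8 | 2.1% | 68.0% |

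Varying the sizes removes nearly all certain knowledge, but only a little of the guessing advantage.

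**5. Cost in balance.** An unfinished block of size 2m can leave the arms at most m apart. The greatest imbalance is therefore 2 with blocks of four, and 4 when the largest block is eight.

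**The case against.** A reader might infer that the research assistants do know a third of allocations in advance. The article does not support that. Certain knowledge needs three things: the block size, the place where blocks begin, and a complete ordered record pooled across assistants. The details withheld from enrolling staff may include the block size. Publication, dated 11 September 2024, does not settle this, because the article does not say how many participants had been randomised by then or what staff had read. This objection stands: 115 is an expectation for a fully informed observer.

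A reader might also see a contradiction between lacking access to the randomisation details and assigning according to the sequence. The two are compatible if REDCap releases one allocation at a time, and nothing says that staff hold the list. What remains is a need for clearer wording.

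The route to bias is also narrow. Eligibility is self-assessed (section 4.2). T1, including a week of accelerometer wear, comes before allocation, so the order depends largely on when participants finish. The primary outcome is device-measured. The model includes T1 steps, and adjusted models cover T1 characteristics that differ materially (section 4.10). It would therefore be too strong to say that analysis can do nothing. Adjustment does not, however, reach unmeasured motivation, and influence over the timing and completion of T1 remains.

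Finally, a condensed article may leave concealment procedures to the full protocol. That is fair for the procedures, but the block size is a design choice that the article itself states.

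**Conclusion.** The point holds as a vulnerability, not as evidence of bias. With fixed blocks of four in one list, and open allocation handled by the staff who enrol, someone who knows the block size and follows the order could deduce an expected 33% of allocations (about 115 of 345) and guess 71% correctly. Hiding the list does not prevent that deduction.

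The figures assume full knowledge of the block size, of the block boundaries and of all earlier allocations in order. With less knowledge they are lower, and the article does not show how much staff have. Self-assessed eligibility and allocation after T1 limit what could be done with the knowledge, without removing the opportunity. Better concealment costs very little, so this is a cheap improvement.

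**What to change.** For allocations still to come:

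1. Regenerate the remaining list in Stata with randomly varying block sizes, for example 4, 6 and 8, and reload it in REDCap.
2. Withhold the sizes from the staff who enrol, and say so in section 4.8.
3. State in section 4.8 that REDCap releases one allocation at a time once T1 is complete, so that staff never work from the sequence.

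The expected gain is a fall in certain knowledge from 33% to about 2%. The gain in guessing is small, from 71% to about 68%, and should not be oversold. The cost is a new list, an amendment to the text and slightly less exact arm balance. The analysis does not change.

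Simple randomisation would bring guessing down to 50%. At n = 345 the 95% range for the difference in arm sizes is about 1.96 × √345 = 36, that is, arms of roughly 154 to 191, with an efficiency loss of at most about (36/345)² = 1.1% within that range. It would, however, give up the balance over calendar time that blocking provides, so varying blocks are the more moderate change.

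If recruitment is complete, the list cannot be changed. The trial report should then say whether enrolling staff knew the block size and how each allocation was released to them.

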### Data collection, management and analysis

4.9

Participants will be asked to complete three assessments (Table 2).

#### Accelerometer

4.9.1

At T1, T2 and T3, participants will be asked to wear a hip-worn Actigraph wGT3X-BT, GT3X + or GT3X accelerometer for seven consecutive days, as recommended [36,37]. Accelerometers indicate total ambulatory (walking) activity, the physical activity behaviour most likely to be impacted by and most closely aligned to the intervention, via estimation of steps. Accelerometers provide valid and reliable measures of steps, physical activity intensity and duration and sedentary time [[38], [39], [40], [41]]. Minimum wear time criteria to be included in analyses is 8 h/day for ≥ four days with non-wear defined as ≥ 60 min of continuous zero counts [36,37].

Accelerometers will be mailed to participants in padded postage packs. Instructions provided (written and/or verbal) will cover—wearing and returning the accelerometer, research team contact details, diary completion for noting date and time of wear and notable comments (e.g. unwell, forgot to wear) and a video link on correct accelerometer use. Monitors not returned will be followed up via telephone and email until received.

#### Bus trip data

4.9.2

Permission to use participants' Metro smartcard data is an eligibility requirement—this eligibility criteria was not a major participation barrier in *trips4health* (only 12/444 potential participants were either unwilling to get a smartcard or share their smartcard data). Smartcard data will be retrieved for the six months prior to study commencement (for participants with an existing smartcard) to objectively assess participants’ usual bus use and confirm eligibility.

A second use of smartcard data is to determine bus trip target attainment during the 14-week intervention phase, with Metro Tasmania allocating credit to participants meeting the targets—a feasible and acceptable process to participants and Metro Tasmania established in *trips4health* [18]. Bus trip credit will be commensurate with fare type (e.g. Adult, Adult Concession, Child/student; across zones 1–3). Participants will be notified via a weekly email whether they met their target, (any) credit they will receive and the next target.

A final use of smartcard data will be to determine any bus use change within and between the control and intervention groups.

Smartcard data collected will include: smartcard number; date, time and fare amount charged ($) at each boarding.

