## Objectives/Hypothesis

2

The primary hypothesis is: A public transport incentives scheme will increase daily steps (accelerometer-measured) compared to a control group. Secondary hypotheses are: A public transport incentives scheme will increase public transport use (objectively measured) and transport-related physical activity (self-reported) compared to a control group.

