### Study setting

4.1

The study will occur in Tasmania, Australia. Tasmania is an island state with a population of approximately 555,000 (460,344 ≥ 15 years). Public transport is provided predominantly by bus, mostly by Metro Tasmania, with services delivered in three of the main population centres—Greater Hobart (population: 226,653), Launceston (population: 90,953) and Burnie (population: 19,919) [21] (Fig. 1). Tasmania has one of the lowest rates of public transport use in Australia with only 3 % and 3.2 % of employed people 15 years^+^ using public transport to get to work in 2016 and 2021 respectively [9]. Unequal and inequitable access to Tasmanian public transport and limitations in service provision contribute to low patronage [17,22,23]. Further, only 26 % of Tasmanians (15^+^ years) self-reported meeting weekly physical activity targets in 2021 [24].

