### Eligibility criteria

4.2

Potential participants will be screened by online survey or telephone. The self-assessed inclusion and exclusion criteria are listed in Box 1. Those eligible will receive an information sheet and provide online or verbal consent.Box 1Self-assessed inclusion and exclusion criteria**Table undtbl1:** 

Inclusion criteria
• ≥ 15 years
• Tasmanian resident
• sufficient English proficiency to provide informed consent
• possession of a mobile phone and active email address
• ownership of or willingness to obtain a Metro Greencard (travel smartcard)
• willingness to give permission for the researchers to access smartcard data
• currently making no more than five Metro bus trips/week
• able to reasonably access a Metro bus service
• currently making trips by motor vehicle (including motorcycle) that could be made by bus
Exclusion criteria
• intending to move house or work location within the study period whereby a Metro bus service will be inaccessible
• currently engaged in or planning to engage in other public transport incentives program
• pregnancy
• a health condition that prevents walking
• a health condition that prevents bus use
• a planned activity that would prevent bus use for greater than four weeks during the 14-week intervention phase of the 38-week study period (e.g. surgery, extended holiday)Alt-text: Box 1

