### Outcomes

4.4

The primary and secondary outcomes and timing of measures are summarised in Table 2. The primary outcome is change in accelerometer-measured average daily step count (steps/day) over seven days. There are 15 secondary outcomes relating to travel behaviour and perspectives, physical activity, sedentary time (sitting), health, transport behaviour economics and intervention implementation costs.

**Table 2 tbl2:** Primary and secondary outcomes and timing of measures.

Outcome (change in …)	Timing of measure	T1	T1-T2	T2	T3
Primary outcome					
Accelerometer measured steps/day averaged over seven days		X		X	X
Secondary outcomes					
Accelerometer measured minutes/week of physical activity		X		X	X
Accelerometer measured minutes/week of sitting		X		X	X
Smartcard measured bus trips/week			X	X	X
Smartcard measured costs to public transport provider			X		
Self-reported (travel diary) trips/week by mode, frequency and duration		X		X	X
Self-reported (travel diary) commute time/week by mode		X		X	X
Self-reported (survey) perspectives on travel behaviour (e.g. enablers/barriers)		X		X	X
Self-reported (survey) out of pocket transport-related expenses		X		X	X
Self-reported (survey) work productivity		X		X	X
Self-reported (survey) commute time to work/study		X		X	X
Self-reported (survey) commute by mode to work/study		X		X	X
Self-reported (survey) physical activity minutes/week by type (transport, leisure, occupational, domestic, total)		X		X	X
Self-reported (survey) sitting hours/day		X		X	X
Self-reported (survey) body mass index via self-measured height and weight		X		X	X
Self-reported (survey) health		X		X	X

T1/Timepoint 1: Baseline; T2/Timepoint 2: Immediately after completion of the14-week intervention phase (∼week 15); T3/Timepoint 3: Immediately after completion of the 24-week maintenance phase (∼week 39).

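### Card boardings both earn the credit in the intervention arm and measure bus use in both arms, so during the paid 14 weeks the secondary bus-use contrast can be inflated by trips newly put on the card

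*Protocol article*

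**What the plan says.** Section 2 states as a secondary hypothesis that the scheme will "increase public transport use (objectively measured"). The matching outcome in Table 2 is "Smartcard measured bus trips/week", marked for the T1-T2 interval, T2 and T3.

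Section 4.9.2 uses the same card record to "determine bus trip target attainment during the 14-week intervention phase, with Metro Tasmania allocating credit to participants meeting the targets" and, later in the section, for the comparison of the arms: "A final use of smartcard data will be to determine any bus use change within and between the control and intervention groups".

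Section 4.3 pays smartcard credit to the intervention arm only. Table 1 lists 32 trip credits against a summed weekly target increase of 34 trips over weeks 1 to 14, worth up to AUD 184.32 at the adult fare. For controls, section 4.3 provides only the physical activity guidelines. The gift cards in section 4.7 go to participants for completing assessments and do not depend on bus trips.

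Two statements show that bus trips can exist outside the card record. Box 1 admits people already making up to five Metro trips a week on "ownership of or willingness to obtain a Metro Greencard (travel smartcard"), so a current rider may enter without a card. Section 4.1 says: "Public transport is provided predominantly by bus, mostly by Metro Tasmania". Other operators therefore exist, and their trips are not on a Metro card.

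Section 4.9.3 also plans a seven-day travel diary at T1, T2 and T3 that records trips by mode. Table 2 lists it as a separate outcome. The article does not describe it as a check on the card.

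**The concern.** Suppose a participant rides as often as before but now taps a card for trips once paid in another way, or swaps another operator's bus for a Metro bus. The card record then shows more bus use although total public transport use has not changed. While credit is on offer, intervention participants gain from doing this and controls do not. The share of true trips that reaches the record can then differ by arm because of the treatment itself. Randomisation does not protect against this, and a perfect baseline would not remove it.

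Bus use is the first link in the chain from incentive to bus to steps, and the plan calls its measurement objective. The likely direction of the bias favours the intervention, so a change of payment method or operator could be reported as a change in public transport use.

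**Working it through.** **Inputs from the protocol.** 300 analysed participants, 1:1 allocation (150 per arm), two-sided 5% level and 80% power (sections 4.6 and 4.8); standard deviation of log change in bus use 0.390 and detectable increase 13.4% (Table 3); entry ceiling of five Metro trips a week (Box 1).

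**Input not in the protocol (assumption).** u, the share of bus trips not on the Metro card when no payment depends on it. I vary it.

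**Step 1: reproduce the plan's figure.** The standard error of the difference in mean log change is 0.390 × √(2/150) = 0.0450. The detectable difference is (1.960 + 0.842) × 0.0450 = 0.126 on the log scale, and exp(0.126) − 1 = 13.4%. Table 3 reproduces.

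**Step 2: spurious rise with no true change in riding.** Both arms would record a share 1 − u of their trips without payment. If payment moves every off-card trip onto the card in the intervention arm, the apparent ratio is 1/(1 − u). If it moves half, the ratio is (1 − u/2)/(1 − u).

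**Step 3: chance of a significant result for the intervention.** This is Φ[ln(ratio)/0.0450 − 1.960]. It assumes that the Table 3 standard deviation applies to this contrast.

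| u (assumed) | All move: rise | Chance of p < 0.05 | Half move: rise | Chance of p < 0.05 |
|---|---|---|---|---|
| 2% | 1/0.98: 2.0% | 6.5% | – | – |
| 5% | 1/0.95: 5.3% | 21% | 0.975/0.95: 2.6% | – |
| 10% | 1/0.90: 11.1% | 65% | 0.95/0.90: 5.6% | 22% |
| 11.8% | 1/0.882: 13.4% | 80% | 0.941/0.882: 6.7% | – |
| 20% | 1/0.80: 25.0% | >99% | 0.90/0.80: 12.5% | 74% |

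A dash marks a chance not computed.

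**Step 4: in trips.** An artefact as large as the detectable effect needs 1 − 1/1.134 = 11.8% of trips to move. At the five-trip ceiling that is 5 × 0.118 ≈ 0.6 trips a week, and for someone making one trip a week about 0.1.

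**Step 5: timing.** Table 1 ends at week 14. Table 2 places T2 at about week 15 and T3 at about week 39, when no trip earns credit. The money reason acts directly in the T1-T2 interval. It reaches T2 or T3 only through carry-over, such as unspent card credit or a habit of tapping.

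**The case against.** The strongest reply has five parts.

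- **Payment stops at week 14.** This stands. A reader might infer that the bias runs through all of follow-up, but Tables 1 and 2 do not support that. It is direct only in the paid window.
- **The size is assumed.** This stands. The documents give no capture rate, and the 12% case is simply the value that reaches Table 3's threshold. At 5% off-card, or with half of a 10% share moving, the artefact is between 5% and 6%. In trips it is small beside weekly target increases of one to four.
- **A measure not tied to payment is already planned.** True: the diary covers both arms at all three time points, and the detail of a card-to-diary comparison could sit in an analysis plan. What remains is a stated design choice, because the article itself makes the payment meter the between-arm measure and calls it objective.
- **Controls may be told to use their card.** Section 4.8 says staff explain the requirements for each arm, but the wording is not shown. A reader might infer that controls get no such instruction; the article does not establish this either way.
- **Moving to Metro is real behaviour.** It is a real change in Metro use, which the scheme may value. It is not a change in total public transport use, which is what the hypothesis names.

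A hard rule requiring the diary to agree before the hypothesis counts as supported would also go too far. The diary is self-report by unblinded participants who have been given trip targets, and over-reporting would push in the same direction.

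**Conclusion.** The concern holds within limits. In the paid 14 weeks, one record both earns credit in one arm and compares the arms, and the protocol's own eligibility and setting statements allow trips outside that record. The T1-T2 card contrast can therefore overstate the effect on public transport use. Under the assumption of no true change and full movement onto the card, off-card shares of 5%, 10% and about 12% give spurious rises of about 5%, 11% and 13.4%; half movement gives about half of each.

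A reader might infer that any rise in card boardings would be an artefact, or that the trial's main result is at risk. The documents support neither. Much of a rise may be real riding, which is what the intervention aims for; the card alone cannot separate new riding from newly recorded riding. The primary outcome is accelerometer steps, which do not depend on tapping. This is a point about interpreting one secondary outcome, and it is worth a cheap improvement.

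**What to change.** 1. Give both arms the same neutral instruction to use the study card whenever they travel on Metro.
2. Prespecify a by-arm comparison of card boardings with diary-reported bus trips (all operators) in those diary weeks for which card data exist. At T1 this can include only participants who already held a card.
3. Report the T1-T2 card contrast as Metro card boardings, and treat the post-payment T2 and T3 card contrasts as the cleaner evidence on bus use, noting possible carry-over.
4. Show the diary bus-trip contrast beside the card result as a sensitivity check, without a pass/fail rule.

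The cost is one sentence in the participant instructions and one added comparison of data already being collected. There are two downsides. The diary is unblinded self-report covering one week per time point and may itself favour the intervention. The instruction could also slightly prompt bus use among controls, whom section 4.11.1 describes as not being encouraged to ride more; neutral wording limits this but may not remove it.
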